| **Methodology** | Our first co-primary objective is to examine the feasibility of a novel social-emotional learning (SEL) curriculum, called EMPOWER SEL, within beyond 3:30, an after-school program that operates across 20 sites in the greater Toronto area. We will do this by asking after-school program staff in the active intervention arm to complete weekly online fidelity checklists for the duration of the program (16-weeks), complete 34 feasibility, acceptability, and appropriateness of intervention measures (Weiner et al., 2017) after each SEL domain is taught, and attend weekly coaching meetings to support the implementation of the EMPOWER SEL curriculum. Youth will also be asked to complete the acceptability of intervention measure (Weiner et al., 2017) post-intervention.  Our second co-primary objective is to evaluate the efficacy of the EMPOWER SEL curriculum. We will do this by asking youth and after-school program staff to complete SEL competency measures (SSIS-SEL Brief Scale; Elliot et al., 2020) during pre- and post-EMPOWER SEL curriculum data collection.  Our secondary objectives are to assess whether there are changes to youth’s overall functioning and resilience as a result of the EMPOWER SEL curriculum. We will assess this by asking youth to complete the KIDSCREEN-10 (Child Public Health, 2023) and CD-RISC-10 (Connor Davidson Resilience Scale, 2007) measures; and after-school program staff to complete the KIDSCREEN-10 (Child Public Health, 2023) pre- and post-EMPOWER SEL curriculum implementation.  We will conduct a cluster stratified randomized with usual programming control study within the beyond 3:30 after-school program to assess feasibility and efficacy of the EMPOWER SEL curriculum. We will use covariate constrained randomization (Moulton, 2004) to balance the sites based on the class size at each site and facilitators who were a part of the iterative trial in May 2024. There are 20 sites within the beyond 3:30 program, 10 sites will be assigned to the active intervention arm and 10 sites will be assigned to the usual programming control arm.  After the active intervention arm completes implementing the 16-week EMPOWER SEL curriculum, and both intervention and usual programming control arms complete the post-EMPOWER SEL program measures, the study will be completed.  Data collection procedure:   - Quantitative Data: - After-school program staff will be sent a secure link to their respective questionnaires that they will complete via REDCap. Facilitators at each site will complete survey measures about each youth’s social emotional skills and overall functioning before and after the curriculum is implemented for the youth who consent to be in the study. This de-identified data, which means there are no names included, is for the research team only. This data will be grouped and no individual data will be analyzed. The data will be used to compare whether there were changes to youth social emotional learning and overall functioning with program participation.   - Staff will receive a gift card of $30/hour honorarium for participating in each of the pre- and post-EMPOWER SEL curriculum implementation surveys.   - After-school program staff will be sent a secure link to complete the weekly fidelity checklist via REDCap. As an honorarium, there will be a monthly draw for 2 $50 gift cards.   - After-school program staff will be sent a secure link to complete the monthly feasibility measures via REDCap. As an honorarium, there will be a monthly draw for 2 $50 gift cards.   - Two staff from CAMH will attend each site, pre- and post-SEL curriculum data collection, to distribute tablets and read each survey question aloud to the group of youth as they complete their surveys via REDCap. Youth aged 11-14 years will consent to their participation in the study. A pizza party at both pre- and post-EMPOWER SEL curriculum implementation data points will be provided for all youth, regardless of whether they complete study surveys or not. - Qualitative Data:   - Interviews with parents/caregivers post-SEL curriculum implementation. A $15 gift card will be provided as an honorarium for parents/caregivers.   **Measures:**  Social Skills Improvement System – Social Emotional Learning (SSIS-SEL Brief Scale;Elliot et al., 2020) is a 20-item, 4-point Likert-type scale that measures self-awareness, self-management, social awareness, relationship skills, and decision making as a composite score of social-emotional competency. Staff in both active intervention and usual programming arms will complete the SSIS-SEL Brief Scale for each youth they work with (avg. 20 youth/site) pre- and post-EMPOWER SEL curriculum intervention. Youth in active intervention and usual programming arms will complete the SSIS-SEL Brief Scale pre- and post-EMPOWER SEL curriculum intervention.  KIDSCREEN 10 (Child Public Health, 2023) is a 10-item, 5-point Likert-type scale that measures global quality of life. Staff in active intervention and usual programming arms will complete an adapted version of the KIDSCREEN for each youth they work with (avg. 20 youth/site) pre- and post-SEL curriculum intervention. Youth in active intervention and usual programming arms will complete the KIDSCREEN pre- and post-SEL curriculum intervention.  CD-RISC-10 (2007) is a 10-item, 5-point Likert-type scale that measures overall resilience. Youth in active intervention and usual programming arms will complete this measure pre- and post-SEL curriculum intervention.  Acceptability of Intervention Measure (Weiner et al., 2017) is a 4-item, 5-point Likert-type scale that measures a composite acceptability of intervention score. Staff in the active intervention arm will complete this measure every 4 weeks, after each social-emotional domain (self-awareness, self-management, social awareness and relationship skills, decision-making) is taught. Youth in the active intervention arm will complete this measure post-SEL curriculum implementation.  Feasibility of Intervention (Weiner et al., 2017) is a 4-item, 5-point Likert-type scale that measures a composite feasibility of intervention score. Staff in the active intervention arm will complete this measure every 4 weeks, after each social-emotional domain (self-awareness, self-management, social awareness and relationship skills, decision-making) is taught.  Intervention Appropriateness (Weiner et al., 2017) is a 4-item, 5-point Likert-type scale that measures a composite appropriateness of intervention score. Staff in the active intervention arm will complete this measure every 4 weeks, after each social-emotional domain (self-awareness, self-management, social awareness and relationship skills, decision-making) is taught.  One facilitator from each site in the active intervention arm will complete a weekly fidelity checklist that consists of 10 questions that assess adherence and adaptations to the lesson plan structure, facilitator perception of youth engagement, facilitator perception of youth’s generalization of SEL skills, and facilitator self-efficacy.  Notes documenting the weekly coaching sessions will not be systematically analyzed, rather they are taken to inform curriculum refinement and are a part of supporting implementing the SEL curriculum.  The following questions will guide the parent/caregiver interviews: *(1) What are your overall thoughts about the inclusion of the SEL curriculum in beyond 3:30? (2) Have you observed any changes in your child's social-emotional competencies since your child began participating in the SEL curriculum? (3) Is there anything else you'd like to share with us about the inclusion of the SEL curriculum at beyond 3:30?* One parent/caregiver from each site in the active intervention arm will be asked (non-probability convenience sample) to participate in a 30-minute (maximum) interview post-SEL curriculum implementation via Webex.  **Data collection time points:**  *2-weeks pre-EMPOWER SEL curriculum implementation*  - youth and facilitators in the active intervention and usual programming control arms will complete the measures for our second co-primary and secondary objectives.  *Weekly (once EMPOWER SEL curriculum begins)*  - facilitators in the active intervention arm will complete fidelity checklists via REDCap at the end of each week.  - facilitators in the active intervention arm will attend weekly coaching meetings at the end of each week to support the SEL curriculum implementation and collect qualitative information to refine the curriculum.  *Every 4 weeks (when facilitators complete an SEL domain)*  - facilitators in the active intervention arm will complete feasibility, acceptability, and intervention appropriate measures via REDCap every 4 weeks for 16 weeks. Feasibility measures are to be completed when facilitators complete the SEL domain they are teaching.  2*-weeks post-SEL curriculum*  - youth and facilitators in the active intervention and usual programming control arms will complete the measures for our second co-primary and secondary objectives via REDCap. Youth will be asked to complete an additional intervention appropriateness measure. Parents/caregivers in the active intervention arm will be asked to participate in a 30-minute interview. |

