## 5.3 Method for Assigning Participants to Treatment Groups

Study sites will be randomized 1:1 to receive either active intervention or usual programming. Covariate constrained randomization (Moulton, 2004) will be used to balance treatment allocation across two site-level characteristics: (1) anticipated class size (ordinal measure), and (2) whether facilitators who were a part of the iterative trial in May 2024 (binary measure). Given the relatively small number of sites and 3-site level characteristics, standard stratified randomization is not appropriate to balance sites as it may lead to incomplete strata (Ivers et al., 2012).

Covariate-constrained randomization. Briefly, since the site-level covariates will be known prior to the start of the study, we will calculate the covariate imbalance in the two site-level characteristics for all possible treatment allocations of the 20 sites. We then select a subset of treatment allocations that minimizes the covariate imbalance. In order to maintain randomness, the actual treatment allocation will be selected from this selected subset. We will implement the covariate constrained randomization in R using the software provided in Carter and Hood (2008).

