# 7.0 STATISTICAL PLAN

## 7.1 Sample Size Determination

**Sample size considerations**

Sample size and power calculations were performed using Power Analysis and Sample Size Software (PASS; 2024).

Co-primary endpoint 1: Feasibility

Feasibility will be assessed by facilitators in the active intervention arm. We expect N=20 facilitators in total (10 active sites x 2 facilitators per site). A sample size of 20 facilitators achieves an exact binomial 95% confidence interval width = 42.3% for co-primary endpoint 1, assuming the intervention is feasible for 14 out of 20 (70%) facilitators.

Co-primary endpoint 2: Social emotional learning

A sample size of 20 clusters (10 active, 10 usual programming) with an average of 20 youth per cluster achieves 89% power (α=5%) to detect a small to medium effect size of 0.35 between arms in the primary endpoint. We assume the coeffient of variation for the cluster sizes is assumed to be 0.25, and the intracluster correlation (ICC) is 0.01.

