## 7.2 Statistical Methods

1. Co-primary Objectives: Feasibility

   Acceptability, Feasibility, and Appropriateness of Intervention Measures: Descriptive statistics will be used to summarize acceptability, feasibility, and appropriateness of intervention measures. Frequencies and proportions will summarize categorical measures; means, medians, standard deviations and ranges will summarize continuous measures.

The frequency and proportion of facilitators and youth who “completely agree” or “agree” that the SEL curriculum is feasible, acceptable, and appropriate will be calculated, along with exact binomial 95% confidence intervals. We’ve set our progression criteria threshold to 70% for feasibility measures. This means that 70% of facilitators and youth “completely agree” or “agree” that the SEL curriculum is feasible, acceptable, and appropriate. We use a traffic light approach (Mellor et al., 2021) where meeting the set threshold equates to a green light and that the curriculum can proceed into its next phases of testing. Changes to the SEL curriculum are required should the threshold not be met (50%-60% = yellow light, or under 50% = red light). In these cases, a consensus meeting with the EMPOWER collaborative (partners [beyond 3:30 and VOS] and staff, youth, and caregiver advisors) will follow to determine necessary revisions and determine the best way to move forward.

Fidelity checklists: Each of the constructs within the fidelity checklist are measured in one-item and are descriptive in nature. They will be analyzed as such.

1. Co-primary Objectives: Social-Emotional Learning
2. SSIS-SEL Brief Scale

The unit of analysis for the primary comparison is individual youth. Linear mixed models will be used to compare pre-post intervention SSIS-SEL scores between groups assuming the fixed effects of treatment group (EMPOWER vs. Usual Programming), time (0 and 18 weeks post-initiation of intervention, and treatment-by-time interaction. To account for repeated measures, random effects of site and youth will be included in the model.

1. Secondary Objectives (secondary)
2. KIDSCREEN and CD-RISC 10 Measures

A similar statistical approach as for co-primary endpoint 2 (SEL) will be used to compare secondary endpoints between arms.

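### The primary SSIS-SEL model estimates a difference in change; adjusting for the baseline score already collected would be more precise, and the stated 89% power describes a different comparison

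*Protocol*

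**What the plan says.** Protocol Section 7.2, and the Statistical Methodology row of the Clinical Trial Summary, set out the model for co-primary endpoint 2:

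- Comparison: "Linear mixed models will be used to compare pre-post intervention SSIS-SEL scores between groups".
- Fixed effects: "assuming the fixed effects of treatment group (EMPOWER vs. Usual Programming), time (0 and 18 weeks post-initiation of intervention, and treatment-by-time interaction".
- Random effects: "To account for repeated measures, random effects of site and youth will be included in the model".

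The secondary endpoints are to be analysed in a similar way.

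The baseline score exists for both arms: "Youth in active intervention and usual programming arms will complete the SSIS-SEL Brief Scale pre- and post-EMPOWER SEL curriculum intervention" (Clinical Trial Summary). It enters the model only as the outcome at time 0.

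Section 5.3 says that covariate-constrained randomisation "will be used to balance treatment allocation across two site-level characteristics: (1) anticipated class size (ordinal measure), and (2) whether facilitators who" took part in the May 2024 iterative trial. It adds that this is feasible "since the site-level covariates will be known prior to the start of the study". Neither covariate is among the listed model terms.

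Section 7.1 claims 89% power "to detect a small to medium effect size of 0.35 between arms in the primary endpoint", with 10 sites per arm, an average of 20 youth per site, a coefficient of variation of site size of 0.25 and an ICC of 0.01.

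**The concern.** In a randomised comparison with one baseline and one follow-up, a model with a free arm effect at baseline subtracts the whole baseline difference. A baseline-adjusted analysis subtracts only the part that predicts the follow-up score. Both estimate the same effect when the arms are comparable at baseline, but the first carries more noise.

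This matters here for two reasons. The trial uses all 20 of the programme's sites (Section 4.2), so precision cannot be bought by adding sites. And the power statement contains no pre-post correlation, although the power of a test of change depends on it. The same model is carried over to KIDSCREEN-10 and CD-RISC-10, so any loss repeats there.

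**Working it through.** **Inputs.** From Section 7.1: 10 sites per arm, 20 youth per site (200 per arm), effect 0.35 SD, ICC 0.01, coefficient of variation 0.25, α = 5% (taken as two-sided, which reproduces the stated power). From Section 7.2: random intercepts for site and youth. Assumed: pre-post correlation r = 0.3, 0.4 or 0.5. Power is by the normal approximation with known variance components and complete data.

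**Step 1: the stated figure.** Design effect = 1 + ((1 + 0.25²) × 20 − 1) × 0.01 = 1.2025. Effective number per arm = 200 / 1.2025 = 166.3. SE = √(2 / 166.3) = 0.1097. Then 0.35 / 0.1097 − 1.96 = 1.23, which gives 89.1%. The stated 89% is a plain comparison of two means, with no baseline in it.

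**Step 2: the change test under the stated model.** Set the total variance to 1: site 0.01, youth r − 0.01, residual 1 − r. Site and youth intercepts cancel in each youth's change, whose variance is 2(1 − r). The arm difference has variance 2 × 2(1 − r) / 200 = 0.02(1 − r). No 1.2025 inflation applies.

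**Step 3: equal baseline means.** The variance of a site mean is V = 0.01 + 0.99/20 = 0.0595. The pre-post covariance of a site mean is C = 0.01 + (r − 0.01)/20. Let ρ = C/V. The variance of the arm difference is (2/10) × V(1 − ρ²), and its ratio to the change variance is (1 + ρ)/2.

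| r | ρ | Change: variance, SE, power | Equal baseline: variance, SE, power | Variance reduction |
|---|---|---|---|---|
| 0.3 | 0.412 | 0.0140, 0.118, 84% | 0.00988, 0.099, 94% | 29% |
| 0.4 | 0.496 | 0.0120, 0.110, 89% | 0.00897, 0.095, 96% | 25% |
| 0.5 | 0.580 | 0.0100, 0.100, 94% | 0.00790, 0.089, 98% | 21% |

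At ICC 0.05, V = 0.05 + 0.95/20 = 0.0975 and C = 0.05 + (r − 0.05)/20. So ρ = 0.641 / 0.692 / 0.744, and the reductions are 18% / 15% / 13%.

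**Step 4: post score on arm and youth baseline, random site effect.** The baseline slope is driven mainly by differences within sites, so it is about β = (r − 0.01)/0.99. The arm difference then has variance (2/10) × [V(1 + β²) − 2βC] = 0.01005 / 0.00910 / 0.00798. That is 28% / 24% / 20% below change, almost all of the gain in Step 3. At ICC 0.05, with β = (r − 0.05)/0.95, the same formula gives 0.01427 / 0.01220 / 0.01014 against 0.0140 / 0.0120 / 0.0100 for change. The gain is then lost unless the site-mean baseline is also in the model.

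**Step 5: the randomisation covariates.** Added as main effects to the stated model, they leave the interaction SE unchanged: 0.0995 with and without, at r = 0.5, in a layout of 20 sites averaging 20.2 youth. In a post-score analysis at ICC 0.01, the between-site share of the variance is 0.2125 / 1.2025 = 17.7%, which caps what they can remove. If they explained 60% of site variance (an assumption), simulation of a post-score comparison of site means shows a gain of about 2 power points or less. If they explained nothing, the loss of 2 of 18 site degrees of freedom would lower power from 85.5% to 85.0% (t-based).

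**The case against.** **The contrast is inferred.** The protocol does not name the interaction as the primary test. This stands, but the pre-post comparison and the listed terms leave no more natural reading. An SAP might add adjustment; the point concerns the model that the protocol itself writes out.

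**A free baseline mean can be defended.** Section 4.2 has intervention-arm facilitators tell youth about the content at the start of the school year, while Section 3.1 puts the baseline survey in mid-October. Enrolment or baseline ratings could therefore be affected by known allocation. This stands against forcing baseline means to be equal. If enrolment did differ between arms, neither analysis would be assured unbiased.

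**Two stronger readings are tempting.**

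- A reader might apply the 1.2025 design effect to the change score. That gives power of 77% / 83% / 89% and a threshold of r = 0.5. The stated model does not support it, because the site intercept cancels in the change. A site-by-time effect would bring some inflation back, but the protocol specifies none.
- A reader might infer that leaving out the randomisation covariates makes the stated test conservative. In simulations at ICC 0.05, with covariates assumed to explain 60% of site variance, a post-score t-test on site means rejected a true null 2.1% to 2.3% of the time. The change test rejected 4.7% to 5.5%, about nominal. The conservatism belongs to a test that the protocol does not use.

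**Conclusion.** The point holds as one of efficiency. At the protocol's ICC, the change contrast has a variance that a baseline-adjusted difference would cut by about 21% to 29% for r between 0.5 and 0.3. That is worth about 10, 7 and 4 power points at r = 0.3, 0.4 and 0.5. The gain shrinks as r rises and as the ICC rises. The stated 89% does not describe the stated test, which reaches it only if r is about 0.4 or more.

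These sizes rest on an assumed r, a stable site effect, 20 youth analysed at every site, complete data and normal-theory power. They do not show bias or a wrong type I error. Omitting the two site covariates is secondary: adding them aligns the analysis with the design, but their benefit depends on a prognostic strength that the protocol does not give, and it is small at ICC 0.01.

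**What to change.** - State the primary contrast. Model the post SSIS-SEL score on arm and the youth's own baseline score, with a random site effect. Consider adding the site-mean baseline (one further site degree of freedom), which protects the gain if the ICC is well above 0.01.
- Include class size and the iterative-trial indicator in that model. Section 5.3 names two site-level characteristics but later refers to three; reconcile this before fixing the list.
- Use the same form for KIDSCREEN-10 and CD-RISC-10.
- In Section 7.1, state the contrast being powered and the assumed pre-post correlation, with a range.
- A repeated-measures model with equal baseline means is an alternative only if baseline is measured free of knowledge of allocation. In that model the site covariates would need to enter as covariate-by-time terms.

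Cost: analysis wording only, with no new data or visits. The post-score model drops youth without a baseline score. The covariates take at least 2 of 18 site degrees of freedom, more if class size enters as several categories.

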# 8.0 SAFETY AND ADVERSE EVENTS

## 8.1 Definitions

Not applicable

## 8.2 Recording of Adverse Events

We do not anticipate any adverse events for youth, staff, or parents who participate in completing study measures. However, any adverse events will be immediately reported to the REB.

## 8.3 Reporting of Serious Adverse Events

### 8.3.1 Investigator Reporting: Notifying the Sponsor

Not applicable

### 8.3.2 Investigator Reporting: Notifying the REB

Not applicable

### 8.3.3 Sponsor Reporting of Adverse Events: Notifying Health Canada

Not applicable

### 8.3.4 Sponsor Reporting of Adverse Events: Notifying Sites

We do not anticipate any adverse events for youth, staff, or parents who participate in completing study measures. Any adverse events will be addressed on a site-by-site basis.

## 8.4 Reporting of Device Deficiencies

Not applicable

## 8.5 Safety Management Plan

- Youth safety and minimizing experiences of distress during youth involvement in the SEL curriculum will be monitored by beyond 3:30 staff who are already trained to identify youth distress within the context of the beyond 3:30 program. Facilitators will inform their beyond 3:30 administrators as well as the CAMH research team should any youth experience distress during the SEL curriculum implementation. Resources for mental health support will be shared with the youth participant and their parent/caregiver.

